| NUMBER OF PATIENTS            | 120 patients to be included, including 60 patients who could be analyzed for the main objective (calculation based on the results of the pilot study carried out at Rennes University Hospital)                                                                                                                                                                                                                                                                                                                                                                                                                                                                                                                                                                                                                                                                                                                                                                                                                                                                                                                                                                                                                                                                                                                                                                                                                                               |
| THEORETICAL NUMBER OF CENTRES | 4 HUGOPEREN centers (Angers, Nantes, Rennes and Poitiers)                                                                                                                                                                                                                                                                                                                                                                                                                                                                                                                                                                                                                                                                                                                                                                                                                                                                                                                                                                                                                                                                                                                                                                                                                                                                                                                                                                                     |
| RESEARCH DURATION             | 
Length of inclusion period: 39 months
 
Maximum duration of participation for each patient/newborn pair: an average of 4 weeks of follow-up for the mother, and up to 15 weeks for the newborn, i.e. approximately 19 weeks.
 
Maximum total duration of the study: 50 months
                                                                                                                                                                                                                                                                                                                                                                                                                                                                                                                                                                                                                                                                                                                                                                                                                                                                                                                                                                                                                                                                                                                                                |
| EXPECTED BENEFITS             | 
This project should position the CHU de Rennes as the French and European leader in technological and clinical research for obstetric care.
 
 
- Medical perspectives: in the long term, to provide clinicians with a decision-support tool by integrating the proposed indicators into a real-time monitoring system that will enable early diagnosis of chorioamnionitis in preterm PROM in a way that is rapid, non-invasive, reproducible and more effective than existing methods. Improving the performance of this diagnosis would lead to a significant reduction in neonatal morbidity and mortality by avoiding adding the complications of chorioamnionitis to those of prematurity in the case of preterm PROM.
 
- Fundamental perspectives: creation of new signal processing tools, understanding the maturation of rhythms during development.
 
- Industrial perspectives: creation of systems to aid in the medical diagnosis of chorioamnionitis and maternal-fetal infection (patent pending), new methods of monitoring and multiparametric functional explorations.
 
- Research perspectives: final evaluation within 2 to 3 years in a multi-center, randomized, intention-to-treat clinical research project (national PHRC); creation of a study network on the variability of cardiac rhythm control and regulation during development.
 
 |

## **LIST OF ABBREVIATIONS**

|         |                                                                                         |
|---------|-----------------------------------------------------------------------------------------|
| ANOVA   | ANalysis Of Variance                                                                    |
| ASCENT  | Anonymised System for Clinical Experimentation                                          |
| ApEn    | Approximate entropy                                                                     |
| CRA     | Clinical Research Associate                                                             |
| AUDIPOG | Association of Users of Computerised Records in Paediatrics, Obstetrics and Gynaecology |
| CER     | Rennes Ethics Committee                                                                 |
| CHU     | University Hospital Centre                                                              |
| CIC-IT  | Clinical Investigation Centre - Technological Innovation                                |
| CNIL    | National Commission for Information Technology and Civil Liberties                      |
| CRF     | Case Report Form                                                                        |
| CRP     | C-reactive protein                                                                      |
| DFA     | Detrended Fluctuation Analysis                                                          |
| ECG     | Electrocardiography                                                                     |
| ETF     | Transfontanellar ultrasound                                                             |
| FHR     | Fetal heart rate recording                                                              |
| GIRCI   | Interregional Group for Clinical Research and Innovation                                |
| HF      | High frequency                                                                          |
| PAH     | Pulmonary Arterial Hypertension                                                         |
| IGFBP-1 | Insulin-like growth factor-binding protein 1                                            |
| INSERM  | National Institute of Health and Medical Research                                       |
| MRI     | Magnetic Resonance Imaging                                                              |
| LF      | Low frequency                                                                           |
| LTSI    | Signal and Image Processing Laboratory                                                  |
| NICE    | National Institute for Health and Care Excellence                                       |
| NN      | Normal to normal                                                                        |
| PHRC    | Hospital Clinical Research Programme                                                    |
| PNN     | Polynuclear neutrophils                                                                 |
| FHR     | Fetal heart rate                                                                        |
| rMSSD   | root mean square of successive differences                                              |
| ROC     | Receiver operating characteristic                                                       |
| PROM    | Premature rupture of the membranes                                                      |
| WA      | Week of amenorrhea                                                                      |
| SampEn  | Sample entropy                                                                          |
| SD      | Standard deviation                                                                      |
| SDNN    | Standard deviation of NN intervals                                                      |
| TRC     | Trace file                                                                              |
| ULF     | Ultra low frequency                                                                     |
| UMR     | Joint Research Unit                                                                     |

|     |                        |
|-----|------------------------|
| USB | Universal Serial Bus   |
| VCT | Short-term variation   |
| VLf | Very low frequency     |
| HRV | Heart rate variability |

## **1. GENERAL INFORMATION**

### **1.1. Title**

Computerized analysis of fetal heart rate variability for early detection of chorioamnionitis in preterm premature rupture of membranes

## 2. RATIONALE FOR THE STUDY

### **Preterm premature rupture of the membranes and early detection of chorioamnionitis**

Chorioamnionitis is an inflammation or infection of the ovarian cavity, usually of bacterial origin. It occurs secondary to premature rupture of the membranes (PROM) in the majority of cases (1).

PROM is defined as the opening of the water sac twelve hours or more before the onset of labour. The diagnosis is primarily clinical, with visible discharge of amniotic fluid on clinical examination. In case of doubt, diagnosis is facilitated by the use of tests, of which the most sensitive and specific currently is the detection of IGFBP-1 in vaginal discharge (2).

Preterm PPROM (< 37 weeks' amenorrhea) is a major public health problem. It accounts for 2 to 3% of pregnancies and around a third of premature deliveries, i.e. more than 20,000 births a year in France. (3-5). In addition to prematurity, the neonatal prognosis in cases of preterm PROM is directly influenced by the presence of chorioamnionitis, estimated to be present in between 15 and 36% of cases, according to (6).

Chorioamnionitis is responsible for an increase in neonatal morbidity and mortality in case of premature delivery. The inflammatory/infectious phenomena induced by chorioamnionitis increase the frequency of respiratory distress, infectious pulmonary pathologies (pneumopathies, alveolitis), necrotizing enterocolitis, periventricular leukomalacia and intracranial hemorrhage, regardless of prematurity. (6-8). Chorioamnionitis also increases the risk of white matter disease leading to cerebral palsy. This relationship has been extensively documented *in vitro*, in experimental animal studies and in observational human studies (9-13).

There are two main definitions of chorioamnionitis in the literature:

- the most widely accepted is histological, where pathological examination of the placenta reveals chorionic inflammation (infiltration of neutrophils in the chorionic plate). (1). The associated inflammation of the umbilical vessels (funiculitis), caused by the fetal inflammatory response, is a serious factor. (14). The disadvantage of this definition in current clinical practice is the retrospective nature of the diagnosis.
- clinical chorioamnionitis, characterized by the appearance of clinical signs suggestive of inflammation/infection of the uterine cavity and/or fetus.

After 34 weeks' amenorrhea (WA), there is no consensus on the appropriate course of action to be taken between expectant care with monitoring or a decision to give birth. However, before 34 WA, the management of preterm PROM consists of expectant care with close maternal-fetal monitoring in a high-risk pregnancy unit of a level appropriate to the gestational age. (15). On the other hand, if signs of chorioamnionitis are detected, the pregnancy should be terminated and the baby should be delivered urgently (16).

The strategies used to reduce the risk of chorioamnionitis in cases of preterm PROM are, on one hand, the systematic prescription of antibiotics and, on the other, close clinical and biological monitoring to detect its

occurrence as early as possible.

However, there is currently no specific marker for the early detection of chorioamnionitis:

- the clinical signs of chorioamnionitis are inconstant, variable, non-specific and usually occur at an advanced stage of infection (uterine contractions, hyperthermia, maternal and/or fetal tachycardia, uterus painful to palpation, foul amniotic fluid). (17).
- the positive predictive value of biological markers used in routine clinical practice is very low, particularly for CRP and hyperleukocytosis, which are the most widely used in France. The measurement of certain cytokines seems promising, but is still experimental and is not the subject of large series. Furthermore, although the sensitivity of these cytokines is interesting, none of them is specific for fetal or intra-amniotic infection (18).

A study carried out at Rennes University Hospital (Appendix 2) has shown for the first time that analysis of fetal heart rate (FHR) variability is a promising avenue of research in this indication.

### **The study of fetal and neonatal heart rate variability: a new avenue of research for the early detection of chorioamnionitis and maternal-fetal infection in preterm PROM**

The study of heart rate variability (HRV) provides a non-invasive approach to the activity of the autonomic nervous system. HRV is generally calculated by analyzing the beat-to-beat time series (RR intervals) of ECG.

Various methods of analyzing heart rate variability have been proposed and many parameters have been extracted from them:

- linear analysis, which breaks down into :
  - o Time-domain analysis with calculation of SD, rMSSD parameters
  - o Frequency-domain analysis, where power is measured in pre-determined bands called LF, HF, VLF
- non-linear analysis where different indices are estimated for example from the Poincaré plot (SD1, SD2) or directly from time series such as the entropy ApEn, SampEn, DFA- $\alpha$ 1 (see Appendix 1)

The diagnostic and prognostic applications of HRV studies are numerous, both in adults (sudden death, atherosclerosis, heart failure, sleep apnoea syndrome, diabetic neuropathy) and in adults (sudden cardiac death, atherosclerosis, heart failure, sleep apnoea syndrome, diabetic neuropathy) (19) or in neonatology: sudden infant death syndrome (20) late neonatal infection. It is in fact possible to identify the occurrence of late neonatal infections in premature newborns (over 3 days of life) by analyzing the complexity of the cardiac rhythm and characterising cardiac decelerations. Sepsis in premature newborns is associated with a drop in approximate (ApEn) and sample (SampEn) entropy, a reduction of heart rate variability and transient decelerations (21-24). This monitoring of heart rate characteristics is simple, non-invasive and rapidly available (it requires only 30 minutes of recording of the neonatal electrocardiogram). It is already used routinely in neonatology and has been shown to reduce mortality in low-weight infants (25).

In order to optimize the analysis of fetal HRV and by analogy with the adult and newborn, the acquisition of the fetal ECG non-invasively has been the subject of much work in recent years. This technique is difficult because of the size of the fetal heart and the need for significant signal processing to dissociate the fetal ECG from the maternal ECG. Recent studies have shown that analysis of HRV is only possible on less than 10% of the recording, and is even virtually impossible between 30-34 SA due to the presence of the *vernix caseosa*, which electrically

isolates the fetus, causing significant attenuation of the fetal ECG signal (26). Thus, the most commonly used tool in obstetrics remains the collection of the cardiac signal by ultrasound. Fetal heart rate (FHR) recording is obtained by Doppler by averaging several fetal cardiac cycles.

During pregnancy, the visual study of the fetal HRV is one of the major criteria in the analysis of the FHR, as a first-line examination for assessing fetal well-being, in particular in the monitoring of preterm PROM. Nevertheless, the visual interpretation of the FHR is unreliable, apart from strictly normal rhythms and highly pathological rhythms with numerous decelerations. Several studies have demonstrated the extent of both inter-observer and intra-observer variation in the analysis of the FHR (27,28). A computerized analysis of the FHR, attempting an objective approach to fetal HRV via the measurement of various parameters, has therefore been developed and marketed since 1989 in the form of the OXFORD® 8000 then 8002 (29). It can be used to calculate:

- Basal heart rate: corresponds to the average FHR during the trace, without acceleration or deceleration.
- accelerations and decelerations: deviations from the baseline
- episodes of high and low variation: these episodes are defined as any part of the recording where, relative to the baseline, the variation in amplitude over one minute is greater than 32 ms (high variation) or less than 30 ms (low variation) for 5 to 6 consecutive minutes. Episodes of high variation are associated with active fetal sleep, while episodes of low variation are associated with quiet sleep.
- short-term variation (STV): measures "micro" fluctuations in fetal heart rate and cannot be measured with the naked eye. It is independent of the baseline. STV is measured by dividing each minute of the trace into 16 sections of 3.75 seconds. The average pulse interval of each section is calculated and the change in these average values from one section to the next determines the STV.

Our previous single-center study carried out at the University Hospital of Rennes (Appendix 2, data not yet submitted for publication, pending patent registration) on a cohort of 23 patients with preterm PROM showed for the first time that analysis of the variability of the fetal heart rate (FHR) via Doppler collection of the cardiac signal is a promising avenue of research for screening for chorioamnionitis.

Certain parameters of FHR variability are modified in cases of histologically proven chorioamnionitis. These changes include an increase in baseline heart rate ( $p=0.02$ ), an increase in episodes of low variation ( $p=0.04$ ), a decrease in short-term variation ( $p=0.003$ ) and episodes of high variation ( $p < 0.001$ ) in the last recordings made before birth (spontaneous or induced) in cases of chorioamnionitis. The index of episodes of high variation (ratio of the mean number of episodes of high variation in the last two recordings to the previous four) appears to be a promising tool for the early diagnosis of chorioamnionitis in preterm PROM (sensitivity 90%, specificity 84.6%, positive predictive value 71.5%, negative predictive value 95.2%, area under the curve = 0.88, 95% confidence interval 0.73-100). These data are in line with those observed in cases of neonatal infection and are consistent with the underlying pathophysiological mechanisms (loss of variability, reduced foetal adaptability in response to the placental infectious/inflammatory stimulus).

These results therefore suggest that a prospective study should be carried out to test this index and to confirm the results for all the cardiac signals collected during the monitoring of preterm fetuses.

## **Conclusion**

Early detection of chorioamnionitis in preterm PROM is a major challenge in obstetric research, and an effective diagnostic tool is still lacking. If the results of our pilot study are confirmed, the integration of these markers of HRV into real-time monitoring would meet this objective. Such a simple, easily accessible, reproducible and non-invasive device would provide clinicians with an aid to clinical decision-making (fetal extraction) that would reduce neonatal morbidity/mortality by avoiding adding the complications of chorioamnionitis to those of prematurity at the time of birth in the case of preterm PROM.

### **3. OBJECTIVES**

#### **3.1. Main objective**

The main objective is to measure the diagnostic value of the index of episodes of high variation of the fetal heart rate (ratio between the average of the number of episodes of high variation of the last two recordings and the four preceding ones) for the detection of histologically proven chorioamnionitis in preterm PROM.

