#### **4.3. Exclusion criteria for the main objective**

Delivery within 48 hours of PROM (clinical situation not allowing calculation of the index of episodes of high variation or modelling of changes in HRV analysis parameters).

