### 7.2. Research process

Inclusion will be prospective: any pregnant patient with a singleton pregnancy hospitalized for PROM between 26- and 34-weeks' gestation will potentially be included in the study.

Doppler recording of the FHR signal will be prospective from inclusion, as part of the routine of fetal well-being monitoring. Analysis of HRV parameters (index of episodes of high variation, linear and non-linear analysis) will be carried out using Matlab® software without the knowledge of the nursing staff. The algorithms for calculating these parameters have already been developed by the Signal and Image Processing Laboratory.

Clinical data will be collected prospectively in a relational events database. It will cover maternal, placental and neonatal data.

The Doppler data from the FHR signals, anonymized beforehand, will be stored progressively on a computer dedicated to the study. A copy of the signals acquired will be made regularly on the CIC-IT's secure server via the ASCENT system (Anonymized System for Clinical experimentation: <https://ascent.univ-rennes1.fr/>) and stored progressively on a database dedicated to the study.

In addition, a joint protocol has been drawn up with the investigating centres, setting out in particular the procedures for fetal heart rate recordings. This protocol does not significantly modify the current practices established in these centres, which are already harmonized.

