### Birth

The following data are collected during this visit:

- mode of delivery and reason (in particular, suspicion of clinical chorioamnionitis) except if spontaneous labour: spontaneous labour, induction, emergency caesarean section
- context of onset of labour: maternal fever, changes in amniotic fluid, uterine contractions, abnormalities in the FHR (visual or computerized)
- Mode of delivery: vaginal delivery, instrumental vaginal delivery, caesarean section

- Birth weight (expressed in absolute value and percentile according to AUDIPOG reference curves)
- Arterial pH and lactates at the umbilical cord, base excess, PCO2,
- How the child is discharged (resuscitation, routine care, intensive care, post-natal care)
- Neonatal death: date, time and autopsy result if performed

Post-natal period (2 days to 15 weeks)

The following data are collected during this period:

- within 72 hours of birth:
  - neonatal biological data: CRP (all), Procalcitonin, peripheral bacteriological samples and blood cultures, blood glucose (random)
  - neonatal clinical data :
    - respiratory: surfactant, ventilation methods
    - cardiovascular: PAH, use of vasopressin amines
    - blood: anaemia (haemoglobin), jaundice (asat, alat, direct and conjugated bilirubin)
    - assessment of suspected maternal-fetal infection: definite, probable or possible according to the criteria of the National Institute for Health and Care Excellence (NICE guidelines CG149)
    - digestive/hepatobiliary: ulcerative enterocolitis with modified Bell stage
  - cardiac variability data: storage of the neonatal ECG (1 recording of one hour in the first 48 hours, then once a week until discharge from hospital)
- remotely:
  - anatomopathological examination of the placenta using a standardized grid to collect information for identifying chorioamnionitis (25,26)
    - acute chorioamnionitis (maternal inflammation)
      - stage 1: infiltrate of neutrophils (PNN) in the roof of the interventricular chamber
      - stage 2: stage 1 + PNN infiltrate in the chorionic plate
      - stage 3: stage 2 + necrosis of PNN and/or amniotic cells
    - foetal inflammatory reaction
      - stage 1: vessels of the chorionic plate and/or umbilical vein
      - stage 2: stage 1 + umbilical artery
      - stage 3: stage 2 + diffusion in Wharton's jelly
    - presence of placental infarcts (old and/or recent) with percentage of placental surface affected (<10%, between 10 and 30%, >30%)

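### The index appears to be evaluated only at the end of pregnancy, with no accuracy estimate at a stated time before delivery, so the primary analysis does not test early detection

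*Protocol*

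**What the plan says.** - **Index.** Section 3.1 defines it as the "ratio between the average of the number of episodes of high variation of the last two recordings and the four preceding ones". It names no reference point for *last*.
- **Pilot.** Section 2 reports the changes seen "in the last recordings made before birth (spontaneous or induced) in cases of chorioamnionitis" and introduces the index in the next sentence. The Summary does the same.
- **Exclusion.** Section 4.3 leaves out deliveries within 48 h of membrane rupture, as a "clinical situation not allowing calculation of the index of episodes of high variation".
- **Claim.** The title is "Computerized analysis of fetal heart rate variability for early detection of chorioamnionitis in preterm premature rupture of membranes". The conclusion of Section 2 says that, if the pilot is confirmed, "the integration of these markers of HRV into real-time monitoring would meet this objective", and presents the tool as an aid to the decision to deliver.
- **Reference standard.** Disease status is placental histology. Section 2 concedes: "The disadvantage of this definition in current clinical practice is the retrospective nature of the diagnosis".
- **Delivery.** Section 2 says that signs of chorioamnionitis lead to urgent delivery. Section 7.2 (Birth) records suspected clinical chorioamnionitis as a reason for delivery, and lists "abnormalities in the FHR (visual or computerized" among the contexts in which labour began.
- **Analysis.** Section 9 plans the AUC, sensitivity, specificity and the two error rates. It also plans an exploratory comparison of monitoring blocks with and without chorioamnionitis, and a repeated-measures ANOVA with gestational age and disease status as factors.

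**The concern.** A marker supports early detection if it discriminates while a decision is still open. Here the test result appears to be read on the last six recordings before birth, and which six those are is known only once the baby is born. In recognised cases, overt infection can set the end of the window, because recognition leads to delivery. A good AUC could then reflect late disease, or labour if recordings in labour count, rather than an early change. Section 2 faults clinical signs for appearing at an advanced stage. An index read only at the end of pregnancy cannot be shown to escape the same criticism.

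**Working it through.** **1. What does *last* refer to?** Section 3.1 is silent. Section 2 and the Summary speak of the last recordings before birth immediately before presenting the index. The exclusion in Section 4.3 makes sense if recordings must accumulate before birth. No other anchor appears: no fixed gestational age, time since rupture, rolling window or interval before clinical diagnosis. Birth is the natural reading, but it is an inference.

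**2. Can the end of the window depend on the disease or the trace?** On the disease, yes: recognised signs lead to delivery (Section 2). On the trace, indirectly: Section 2 treats visual reading of variability as a major part of monitoring after rupture, and Section 7.2 records heart-rate abnormality as a context of labour.

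**3. Does any planned analysis fix a time before delivery?** The accuracy measures in Section 9 carry no time reference. The ANOVA runs on gestational age, so two patients at the same gestational age may be hours or weeks from birth. The block comparison is not tied to time before delivery. Histology gives no onset date, so timing can come only from when the index is read.

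**4. How long could the lead time be?** The protocol gives no such figure. Section 7.2 says only: "Doppler recording of the FHR signal will be prospective from inclusion, as part of the routine of fetal well-being monitoring". Assume k evenly spaced recordings a day, continuing until birth:
- interval, and the longest gap from last recording to birth = 24/k h
- span of six recordings = 5 × 24/k h
- time from first recording of the window to birth needed for a lag of L hours = L + 5 × 24/k h

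| k (assumed) | Last recording before birth, at most | Six recordings span | Needed for 24 h lag | Needed for 48 h lag |
|---|---|---|---|---|
| 1 | 24 h | 120 h | 144 h | 168 h |
| 2 | 12 h | 60 h | 84 h | 108 h |
| 3 | 8 h | 40 h | 64 h | 88 h |
| 4 | 6 h | 30 h | 54 h | 78 h |

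**5. How many cases are there?** Section 8 gives 60 analysable patients (120 × 0.5) and 15% prevalence: 60 × 0.15 = 9 cases and 51 non-cases.

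Section 8 states 95% power for the t-test on the index. With means 3.82 and 1.18 and SD 1.7, the noncentrality is 2.64 / (1.7 × √(1/9 + 1/51)) = 4.30. On 58 degrees of freedom this gives 98.8%, so the stated figure is conservative. It concerns a difference in means in one window and says nothing about timing.

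For precision, take the pilot AUC of 0.88 and the Hanley–McNeil formula. A/(2 − A) = 0.7857, 2A²/(1 + A) = 0.8238 and A² = 0.7744. The variance is (0.1056 + 8 × 0.0113 + 50 × 0.0494)/(9 × 51) = 0.0058, so the SE is 0.076 and the 95% half-width is 1.96 × 0.076 = 0.15. That is before any patient drops out of a lagged window.

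**The case against.** Several stronger readings are tempting, and the documents do not support them.

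- **A reader might infer that the index can be computed only after delivery.** It cannot be put that way. The ratio can be formed on any six consecutive recordings; only the study's evaluation window is fixed in retrospect.
- **A reader might infer that there is almost no lead time.** The hours above rest on an assumed frequency. A joint protocol governs the recordings, and Appendices 2 and 4 are not shown.
- **A reader might infer that the tested index itself triggers delivery.** The Summary and Section 7.2 say that the computed analysis is kept from nursing staff. What remains is indirect dependence through the visible trace.
- **A reader might infer that nothing looks at earlier recordings.** Section 7.2 counts the index among the variability parameters, Section 9 compares parameters across blocks and over gestational age, and Section 5.2 plans to model their evolution. What is missing is narrower: accuracy at a stated time before delivery.
- **A reader might infer that the study cannot support early detection.** Serial recordings are kept from inclusion, so the data could address it.

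It is also fair to say that Sections 3.1 and 5.1 speak of detection, not early detection, that real-time use is conditional on confirmation, and that the Summary defers final evaluation to a later randomised project. The stated objective can therefore be met as planned.

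These arguments narrow the point but do not remove it. The title and rationale make the early claim, and the planned accuracy analysis does not address it.

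**Conclusion.** The point holds in limited form. On the natural reading, the index is evaluated on the last six recordings before birth, a window whose end can depend on recognised disease or a visibly abnormal trace. With no accuracy estimate at a stated time before delivery, the primary analysis supports discrimination at the end of pregnancy. It does not by itself support the early detection of the title and rationale.

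This rests on inferring birth as the anchor. The size of the lead time is unknown: at most 24 to 6 h under the assumed schedules of 1 to 4 recordings a day. The primary objective is not invalidated. A SAP, which is not shown, might add a lagged analysis, but the index definition and the claim are set in the protocol and should be aligned there.

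**What to change.** 1. In Section 3.1, state that *last* means last before delivery, and whether recordings made in labour count.
2. In Section 9, add a pre-specified secondary analysis that recomputes the index on windows whose last recording ends at least 24 h, and at least 48 h, before delivery. Report the AUC, and sensitivity and specificity at whatever cut-off is fixed for the primary analysis (the protocol text gives no value), with confidence intervals and the number of cases in each window.
3. Limit any early-detection conclusion to these lagged results; otherwise describe the finding as detection at the end of pregnancy.
4. Report results by reason for delivery descriptively only. Excluding deliveries for suspected chorioamnionitis would select on the outcome and remove cases from about 9.

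No new data are needed: Sections 7.2 and 11.8 provide for storing the signals, and the reason for delivery is already collected. The cost is precision and interpretation. Patients with short latency drop out of the lagged windows, so intervals would probably be wider than the ±0.15 shown for a full set of 9 cases. Because histology gives no onset date, a negative lagged index may mean disease not yet present rather than disease missed.
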